## Abstract

**Background:**

Polycystic ovary syndrome (PCOS) is one of the most common endocrine diseases with major reproductive and metabolic complications with an impact on public health. Hyperandrogenism and chronic inflammation have been suggested as the leading cause of pathophysiology and clinical manifestations associated with PCOS. It seems that the altered expression of genes involved in the synthesis of pro-inflammatory cytokine and androgens contribute to the promotion of PCOS.

**Objective:**

This trial aims to determine the effects of dietary approaches to stop hypertension (DASH) and standard diets with and without curcumin supplementation on the gene expression of interleukin -1 alpha(IL1α), 5α reductase and androgenic and glycemic profile among PCOS patients, who are candidates for in vitro fertilization.

**Materials and Methods:**

96 infertile women with PCOS, aged 18-40 yr, will participate in this randomized, placebo-controlled clinical trial. Based on treatment conditions and body mass index, the participants will be randomly divided into 4 equal groups using a randomized block design. They will receive a DASH or standard diet containing 52% carbohydrate, 18% protein, and 30% total fat, with the same prescribed sodium, plus 500 mg twice daily curcumin or placebo for 12 wk. The mRNA expression of *IL-1
α

*, *5
α

* reductase, and androgenic and glycemic profiles will be measured at baseline and at the end of the study.

**Conclusion:**

Concomitant administration of DASH diet and curcumin supplementation may reduce *IL-1
α

*, *5
α

* reductase gene expressions, and improve glycemic and androgenic profiles.

## 1. Introduction

Polycystic ovary syndrome (PCOS) is an endocrine disorder that can lead to major reproductive and metabolic complications, including infertility and insulin resistance. According to the 2003 Rotterdam criteria, the prevalence of PCOS in women of reproductive age is 4.4-18.6% (1). The Rotterdam consensus is the most widely accepted diagnostic criteria (2), by which women must meet at least 2 of the 3 following criteria: 1) confirmation of polycystic ovary by ultrasound; 2) clinical or biochemical hyperandrogenism; and 3) ovulatory dysfunction (oligo/anovulation) (3).

Hyperandrogenism and chronic inflammation have been suggested as the leading causes of pathophysiology and clinical manifestations of PCOS (4). Biochemical hyperandrogenism is defined as a high concentration of testosterone and a high level of free testosterone and free androgen index (3). Hyperandrogenism may be caused by increased 5α-reductase activity, a key enzyme with an essential role in regulating the peripheral conversion of testosterone to the most active androgen, 5α-dihydrotestosterone (5). The findings showed that the activity of 5α-reductase increased in PCOS, and this high activity is related to insulin resistance (6). There are 2 isozymes of 5α reductase, encoded by the 5α-reductase type1 and type2 genes (7). Findings from an animal study suggest that insulin-mediated changes in 5α-reductase type1 messenger ribonucleic acid (mRNA) expression can negatively affect the follicle development and ovulation (8). In addition, mild chronic inflammation, independent of obesity, has been confirmed in PCOS patients (4). One of the most important inflammatory mediators, interleukin-1 (IL-1), is a multifunctional cytokine with 3 different cytokines, including cytokines (α, β) and an IL-1 receptor antagonist. *IL-1
α

* gene polymorphism can be associated with PCOS and affect ovulation, fertilization, and implantation (9, 10).

Given the potential effects of chronic inflammation on the pathogenesis of PCOS through the pathway of insulin resistance and hyperandrogenism (11), new strategies have been proposed to improve the clinical symptoms of PCOS. According to evidence-based recommendations, lifestyle intervention (various components including diet, exercise, and behavioral approaches) is recommended (3).

The dietary approaches to stop hypertension (DASH) diet has been suggested as an effective treatment option (12). DASH diet, as a low-glycemic diet (13), with a high concentration of antioxidants, can have beneficial effects in reducing insulin resistance (14), inflammation (15), and free androgen index (16). This diet is rich in vegetables, low-fat dairy products, fruits, whole grains, poultry, fish, and nuts, but is limited in foods high in sodium, cholesterol, saturated fat, red and processed meat, refined grains, sweets, and sugary drinks (12). In the last decade, the antioxidative effects of plant polyphenols have been considered (17). Indeed, among natural phenols, the therapeutic properties of curcumin have been further investigated (18). Curcumin (diferuloylmethane) is a lipophilic yellow pigment extracted from turmeric rhizomes (*Curcuma longa L.*) (19). Curcumin supplementation improves glycemic control and lipid metabolism, and reduces radical oxygen species in PCOS patients (20, 21).

The anti-inflammatory and antioxidant benefits of both the DASH diet and curcumin have been demonstrated by meta-analysis results (15, 22). Therefore, we plan to investigate the effect of the DASH diet in combination with curcumin supplements on *IL-1
α

* and *5
α

* reductase gene expressions and improvement of insulin resistance and hyperandrogenism.

## 2. Materials and Methods

### Trial design and study setting

This randomized, placebo-controlled clinical trial will be conducted on PCOS women candidates for in vitro fertilization (IVF), using a convenience sampling method. Participants in a 2
×
2 factorial design will be randomly divided into 4 parallel treatment groups using block randomization: (1) curcumin supplement + DASH diet (2) curcumin supplement + standard diet (3) placebo + DASH diet, and (4) placebo + standard diet. The follow-up duration will be 12 wk. The study will be conducted at the Yazd Reproductive Sciences Institute, Shahid Sadoughi University of Medical Sciences, Yazd, Iran. An overview of the study is presented in figure 1.

### Eligibility criteria 

Infertile women with PCOS (according to the Rotterdam criteria) (2) who were candidates for IVF treatment, without a previous history of IVF, will be included in this study. Eligibility criteria included body mass index (BMI) between 18.5-25 and BMI 
≥
 25 kg/m² and aged between 18–40 yr.

The participants must not have any of the following:

Metabolic and endocrine abnormalities including thyroid dysfunction, Cushing's syndrome, diabetes or impaired glucose tolerance, hyperprolactinemia, congenital adrenal hyperplasia, liver disease, cardiovascular disease, kidney disease, hypertension, neurological diseases, any history of mental illness, cancer, autoimmune and inflammatory disorders (rheumatoid arthritis). Taking medications including contraceptives or any other drugs that may affect reproductive physiology (during the 3 months before the study); taking antidiabetic, antiobesity, estrogenic, and androgenic drugs, as well as taking supplements such as vitamin C, vitamin E, and omega-3 because of their anti-inflammatory and antioxidative effects, 3 months before or during the intervention; smoking or exposure to spouse's smoking; alcohol drinking; being pregnant; simultaneous participation in another study. Moreover, unwillingness to cooperate and nonadherence to dietary or supplementary interventions (compliance 
<
 80%), allergy to supplements, and pregnancy of the participant during the study will be considered as drop-out criteria.

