 day of visit), each bottle containing 64 capsules (providing supplement for 1 month and a grace period of 2 days). Administration instructions on taking the pills and what needs to be done in case a dose is missed were set for patients, including taking 2 curcumin/placebo capsules a day (one after breakfast and one after an evening meal with water) and taking the missed capsule the same day. The patients will be monitored for daily supplementations by contacting them via phone interviews and messaging (Eitaa or Bale apps) twice a day. Moreover, daily consumption of supplements/placebos will be recorded in the case report form given to participants. At each follow-up visit, a nutritionist will assess the participants adherence to the diet and supplementation. The number of capsules taken will be calculated by counting the remaining capsules in each bottle. If the number of unused prescription capsules is more than 12 out of 60 capsules per month, for each participant, that patient will be classified in the non-adherent group.

All adverse events including unfavorable and/or unintended signs and any undesirable experience occurring to a patient will be reported in writing to the Medical Ethics Committee and the Data Monitoring Committee of the Shahid Sadoughi University of Medical Sciences, Yazd, Iran. The participants, for whatever reason, can discontinue participating in the research study at any given time before or after signing the consent form. The researcher may also terminate the study to maintain safety and protect the participant from excessive risks and/or to keep the integrity of the research data due to inappropriate follow-up by the participant. In case of termination of the study by the investigator, the reasons for the termination will be explained to the participants.

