### Statistical methods

The values of quantitative variables will be presented as the mean 
±
 standard deviation, and qualitative variables will be expressed as numbers and percentages. The normality of data will be examined by the Kolmogorov-Smirnov test.

The frequency among study groups will be compared using the Chi-square test. Independent sample *t* test and 2-way ANOVA will be applied to estimate the mean of quantitative variable changes and interactions between study groups; Bonferroni correction will be considered for multiple comparisons; and analysis of covariance (ANCOVA) will be used to compare the differences in the mean of quantitative data between the studied groups, while taking into account the influence of possible confounding variables. Before statistical analysis, all data will be checked for accuracy and completeness. All statistical analysis will be conducted using SPSS 22 (SPSS, Inc, Chicago, IL, USA). A p-value 
<
 0.05 will be defined as a statistically significant level.

The “intention-to-treat" and “per protocol analysis" approaches will be performed for data analysis. The “intention-to-treat" analysis considers all participants in their main randomized groups, regardless of whether they follow the prescribed intervention according to the protocol or not, and also ignores non-compliance and withdrawal. Per protocol analysis, which accurately reflects what has been done, will be conducted based on actual adherence to the interventions.

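### Non-adherence below 80% is a drop-out criterion, which conflicts with the promised intention-to-treat analysis and may cost it week-12 outcomes

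*Protocol article*

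**What the plan says.** Three sections of the protocol article deal with a woman who does not adhere.

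- **Eligibility criteria.** The list of drop-out criteria contains "unwillingness to cooperate and nonadherence to dietary or supplementary interventions", with compliance below 80% as the threshold, and continues with "allergy to supplements, and pregnancy of the participant during the study will be considered as drop-out criteria". All of these arise after randomisation.
- **Interventions.** The capsule count sets a cut-off: "If the number of unused prescription capsules is more than 12 out of 60 capsules per month", then "that patient will be classified in the non-adherent group". Nothing here says that she leaves the study.
- **Statistical methods.** The ITT analysis "considers all participants in their main randomized groups, regardless of whether they follow the prescribed intervention according to the protocol or not", and is also to disregard non-compliance and withdrawal. A separate per-protocol analysis is based on actual adherence.

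Three further statements bear on the consequence. The Abstract and the Biochemical measurements section place outcome measurement at baseline and at the end of the 12 weeks only. The Interventions section has bottles issued on days 1, 30 and 60 and adherence judged at each follow-up visit. The Sample size section allows for 20% dropout.

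**The concern.** Under one rule a woman below 80% compliance is a drop-out. Under another she is labelled and stays. Under a third she must be analysed as randomised. Site staff cannot tell from this text whether to call her back at week 12.

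That matters because there is only one post-baseline measurement. A woman dropped after the day-30 or day-60 count, and not recalled, has no post-baseline value for either primary outcome. An analysis plan can choose how to treat a missing value, but it cannot recover a blood sample that was never drawn.

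Removal may also depend on the assigned arm. The Recruitment section accepts that participants may know their diet, so diet adherence can differ between diet arms. Supplement allergy can depend on the capsule. Pregnancy may depend on treatment in infertile women whose hormonal and metabolic profile the interventions aim to improve. If women are lost for such reasons, the comparison is no longer between the groups as randomised.

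**Working it through.** **1. Is it the same threshold?** The capsule rule allows at most 12 of 60 unused: 1 − 12/60 = 0.80. The Eligibility criteria and Interventions sections therefore use one cut-off with two different consequences, drop-out and classification.

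**2. When can it be reached?** Twelve weeks is 84 days. Counts on the first two bottles fall due around days 30 and 60, before the final sample. A shortfall in the third bottle would normally be counted only at or near the end.

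**3. The planned dropout.** The plan states 24 per group, with two-sided α 0.05, 80% power, effect size 1 and 20% dropout.
- Printed formula: n = 2 × (1.960 + 0.842)² / 1² = 15.7, so 16; 16/0.8 = 20.
- t-distribution version: 17; 17/0.8 = 21.25, so 22.

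Neither gives exactly 24. The stated number is on the generous side, and the difference does not affect this point. What matters is that the inflation treats drop-outs as not analysed: 0.2 × 96 = 19.2 women lost, leaving 0.8 × 24 = 19.2 per group. Two-sided t-test power at effect size 1 is 92% with 24 per group and 85% with 19. The issue is who is analysed, not loss of power.

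**4. Size if dropped women are not measured (assumptions, not from the protocol).** Let adherers in an active arm gain 1.0 SD. Let a fraction p of that arm be dropped, keeping a share k of the gain.
- All-randomised effect = 1 − p(1 − k)
- Overstatement when only adherers are analysed = 1/[1 − p(1 − k)] − 1

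| p | k | All-randomised effect (SD) | Overstatement |
|---|---|---|---|
| 0.20 | 0 | 0.80 | 25% |
| 0.20 | 0.5 | 0.90 | 11% |
| 0.10 | 0 | 0.90 | 11% |
| 0.10 | 0.5 | 0.95 | 5% |

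**5. Simulation check (24 per arm, 4,000 runs, two-sided t-test at 5%; assumed inputs).** Correlation means that between adherence and outcome.
- No true effect, 20% removed in both arms by the same mechanism: mean adherers-only difference between −0.001 and 0.005 SD, that is, no bias.
- No true effect, 30% v 10% removed, correlation 0, 0.3 and 0.5: adherers-only bias about 0, 0.09 and 0.15 SD; type I error about 5%, 6% and 8%. The all-randomised analysis stays near 5%.
- True gain of 1 SD in adherers and none in the 20% non-adherers: all-randomised effect about 0.80 SD with power 72–73%; adherers-only about 1.0 SD with power 85–87%.
- As above, but non-adherers keep half the gain: about 0.90 SD against 1.0 SD.

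**The case against.** The strongest reply is that the only section defining analysis sets keeps non-compliers in. It states that ITT takes everyone as randomised, and the Interventions section merely labels women at the 80% cut-off, which fits a per-protocol definition. No section says that a dropped woman goes unmeasured at week 12. Late lapses would often be found when the final sample is due, so such women can still have outcomes.

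Much of this stands, and it rules out three stronger readings.

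- **That ITT cannot be done, or that the two sets become identical.** A reader might infer this from the drop-out list, but it requires that dropped women are never measured, which the text does not say.
- **That per-protocol is given primacy.** The sentence "Per protocol analysis, which accurately reflects what has been done, will be conducted based on actual adherence to the interventions" is loose, since that set is chosen on behaviour after randomisation. Still, it claims no priority and ITT is listed first. Which set is primary, and how missing values are handled, commonly belong in an analysis plan that is not shown, so neither is a fault here.
- **That the termination clause is a second route for removing non-adherers.** Its reason, "to keep the integrity of the research data due to inappropriate follow-up by the participant", concerns poor follow-up rather than non-adherence to diet or capsules, and it speaks of terminating the study. It is weak support.

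The size is also open to challenge. The 20% allowance covers all dropout and gives no share for non-adherence. The 25% figure needs every loss to be a non-adherer with no benefit at all.

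What the reply does not remove is the conflict between the three sections, or the silence on week-12 measurement for a woman who meets a stated drop-out criterion.

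**Conclusion.** The conflict is real and lies in the printed rules. Compliance below 80% is a drop-out criterion in one section, a label in another and irrelevant to the ITT set in a third. The harm is conditional. If women dropped for non-adherence are not measured at week 12, as the dropout allowance suggests but the text does not state, the ITT analysis loses them and moves towards the per-protocol set.

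Under the assumptions shown (1.0 SD gain in adherers, none to half of it kept by dropped women, 10% to 20% of an active arm removed), the all-randomised effect would be overstated by about 5% to 25%. Under no true effect the bias is nil when removal is equal in both arms. It reaches about 0.15 SD, with type I error near 8%, only in the most unequal case tried. The protocol gives no figures that would narrow these ranges. The point merits correction because it concerns conduct, and missed samples cannot be recovered at analysis.

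**What to change.** Reconcile the Eligibility criteria, Interventions and Statistical methods sections:

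1. Remove non-adherence from the drop-out criteria and use the 80% threshold only to define the per-protocol set.
2. Separate stopping the intervention from leaving the study. Whether and when to stop capsules or diet for clinical reasons, including allergy or pregnancy, stays with the investigators.
3. State that every randomised woman is invited for the week-12 blood sample and measurements whatever her adherence, unless she withdraws consent to follow-up.

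The cost is a change of wording and some extra effort to bring back women who would otherwise have been dropped. The estimated effect may also look less favourable, because women with less benefit remain in the comparison.

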### Interventions

Participants will be given 2 capsules of curcumin supplement per day (1 after breakfast and another after an evening meal with water) or 2 placebo capsules of curcumin per day at the same time for 12 wk. Curcumin capsules (BCM95/Curcugreen) and their placebos, with the same texture and appearance, were produced as 500 mg zero size veg capsules by “M/s Arjuna Natural Pvt Ltd., India”. The curcumin supplement was made from dried turmeric rhizomes by extraction with ethyl acetate. *Curcuma longa L. *commonly known as turmeric contains curcuminoids (curcumin, demethoxy curcumin, and bisdemethoxy curcumin) and essential oil of turmeric (ar-turmerone, curlone, and ar-curcumene). Curcuminoids are specific compounds with medicinal properties, of which the most important and active ingredient is the yellow coloring pigment curcumin; Ar-turmerone (the main bioactive components of the *Curcuma longa L*. essential oil), inhibits the P-glycoprotein pathway, thus improving the oral bioavailability and bioactivity of orally administered curcuminoids. BCM-95 was characterized by 95% total curcuminoid complex; the final formulation containing at least 65% curcumin and 86% total curcuminoids; and the essential oil containing not less than 45% ar-turmerone. Each 500-mg capsule contained 475 mg of curcuminoids and the essential oil of natural turmeric. Each placebo capsule contained 500 mg of roasted rice powder. The curcumin capsule actives will be analyzed by HPLC, heavy metals by ICP-MS; residual solvents by GCHS, pesticides by GCMS, and microbial indicators all of which were ensured to be in line with the EU standards (regulation (EC) No 1881/2006; directive 2009/32/CE; regulation (EC) No. 396/2005 and related amendments).

The intervention groups will receive 2 healthy dietary patterns (DASH or standard diet). These diets will be designed in the form of an individual diet containing 18% protein, 52% carbohydrates, and 30% total fat, which will be matched with the macronutrient plan used in the other original trial (23). Dietary programs will be planned after baseline assessments based on the current dietary intakes and body weight of each person. Daily calorie requirements will be estimated by calculating the resting energy expenditure and physical activity levels. If a person was overweight (BMI is 25.0 to 
<
 30.0 kg/m²) or obese (
≥
 30.0 kg/m²), the calculated energy will be reduced by 300 and 500 kcal, respectively. A 12-wk menu plan (7-day cycle menu with 21 meals) at 11 energy levels (1200, 1300, 1400, 1500, 1600, 1700, 1800, 1900, 2000, 2100, and 2200 kcal) for both dietary patterns will be constructed and analyzed. These will be considered as the basis for participants' diets. Nutritionist IV software (diet analysis, module version 3.5.2) will be used to calculate energy, food exchange, percent of kilocalories from macronutrients, and nutrient values in each daily menu plan. DASH diet will be designed with an emphasis on food rich in fiber, magnesium, potassium, calcium, and protein, such as vegetables, fruits, and low-fat dairy products; while foods high in saturated fat and sugar will be limited (12). The amount of sodium prescribed for each diet will be the same (2300 mg per day-approximately 1 teaspoon of salt). Overall, DASH and standard patterns will be designed using similar foods and recipes, but in different amounts, to achieve the specific characteristics of each diet. Both diets will be planned by the study dietitian and reviewed by the Chief investigator.

Participants will receive their specific diet through face-to-face individual counseling, initial assessment, and intervention for 45-60 min with a registered dietitian (follow-up visits for 15-30 min per month). They will also receive a bottle of supplement/placebo (on the 1
${}^{\text{st}}$
 day, 30
${}^{\text{th}}$
 day, and 60
${}^{\text{th}}$
 day of visit), each bottle containing 64 capsules (providing supplement for 1 month and a grace period of 2 days). Administration instructions on taking the pills and what needs to be done in case a dose is missed were set for patients, including taking 2 curcumin/placebo capsules a day (one after breakfast and one after an evening meal with water) and taking the missed capsule the same day. The patients will be monitored for daily supplementations by contacting them via phone interviews and messaging (Eitaa or Bale apps) twice a day. Moreover, daily consumption of supplements/placebos will be recorded in the case report form given to participants. At each follow-up visit, a nutritionist will assess the participants adherence to the diet and supplementation. The number of capsules taken will be calculated by counting the remaining capsules in each bottle. If the number of unused prescription capsules is more than 12 out of 60 capsules per month, for each participant, that patient will be classified in the non-adherent group.

All adverse events including unfavorable and/or unintended signs and any undesirable experience occurring to a patient will be reported in writing to the Medical Ethics Committee and the Data Monitoring Committee of the Shahid Sadoughi University of Medical Sciences, Yazd, Iran. The participants, for whatever reason, can discontinue participating in the research study at any given time before or after signing the consent form. The researcher may also terminate the study to maintain safety and protect the participant from excessive risks and/or to keep the integrity of the research data due to inappropriate follow-up by the participant. In case of termination of the study by the investigator, the reasons for the termination will be explained to the participants.

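### The fixed limit of 12 unused capsules out of 60 per month does not express 80% adherence in the shortened last dispensing period

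*Protocol article*

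**What the plan says.** All of this is in the protocol article.

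- Trial design and study setting: "The follow-up duration will be 12 wk".
- Interventions, dose count: "Participants will be given 2 capsules of curcumin supplement per day", or the matching placebo.
- Interventions, supply: bottles are handed out on days 1, 30 and 60, "each bottle containing 64 capsules (providing supplement for 1 month and a grace period of 2 days".
- Interventions, counting: "The number of capsules taken will be calculated by counting the remaining capsules in each bottle".
- Interventions, limit: "If the number of unused prescription capsules is more than 12 out of 60 capsules per month", the woman goes into the non-adherent group.
- Eligibility criteria: the drop-out criteria include "nonadherence to dietary or supplementary interventions (compliance" below 80%).
- Statistical methods: the per-protocol analysis "will be conducted based on actual adherence to the interventions".

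The article does not say that the four grace capsules are subtracted before the comparison, that the limit is scaled to a shorter last period, or that leftovers are carried over or averaged across bottles.

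**The concern.** A limit of 12 in 60 is evidently meant to be the 80% criterion in capsule form. It is stated as a fixed number per month, but three monthly bottles span 90 days and treatment stops at 84. The last period is therefore five or six days short of a month, while both the bottle and the limit keep their full-month size. Unused capsules then include some that were never due.

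At stake is who counts as adherent at the final visit, and so who can enter the per-protocol set. If the same count is used for the drop-out criterion, it also affects who is treated as a drop-out. The Sample size section plans 24 women per group and allows 20% dropout, which is 0.20 × 24 = 4.8 women per group, so a few misclassified women would matter. There is a second risk: if staff correct for the short period informally, different assessors may apply different limits.

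**Working it through.** **Inputs.** Two capsules a day; 12 weeks = 84 days; bottles of 64 on days 1, 30 and 60; limit of more than 12 unused of 60 per month; compliance criterion of 80%.

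**1. The plan's own figures.** Bottle: 2 × (30 + 2) = 64. Limit: 12/60 = 20% unused, so 48/60 = 80% taken. Both reproduce for a 30-day month.

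**2. Total supply.** Dispensed 3 × 64 = 192. Due 2 × 84 = 168. Left at full intake: 192 − 168 = 24.

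**3. Length of the last period.** The 84 days split as 30 + 30 + 24 or as 29 + 30 + 25, depending on whether the visit day belongs to the old or the new bottle. Capsules due in the last period: 2 × 24 = 48 or 2 × 25 = 50.

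**4. The fixed limit under three readings.** A flag needs at least 13 unused.

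| What is compared with 12 | 30-day month (60 due) | Last period, 25 days (50 due) | Last period, 24 days (48 due) |
|---|---|---|---|
| A. Everything left in the bottle of 64 | 64 − 60 = 4 left at full intake; flagged from 9 missed, 51/60 = 85% | 64 − 50 = 14 left; flagged with none missed | 64 − 48 = 16 left; flagged with none missed |
| B. Capsules left out of 60 (grace capsules removed) | 0 left; flagged from 13 missed, 47/60 = 78.3% | 60 − 50 = 10 left; flagged from 3 missed, 47/50 = 94% | 60 − 48 = 12 left; flagged from 1 missed, 47/48 = 97.9% |
| C. Due doses not taken | flagged from 13 missed, 78.3% | 12 missed passes, 38/50 = 76% | 12 missed passes, 36/48 = 75% |

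In the full month, readings B and C agree with 80%. In the last period none of the three does.

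**5. A 29-day first period (58 due).** Reading A leaves 64 − 58 = 6 and flags from 7 missed, 51/58 = 87.9%. Reading B leaves 60 − 58 = 2 and flags from 11 missed, 47/58 = 81.0%, which is close enough to 80% to ignore.

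**6. Carry-over.** If a woman finishes each old bottle before opening the next, all 24 spare capsules end up in the third bottle. On a base of 60 per bottle the spare total is 180 − 168 = 12.

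**7. What 80% means in the last period.** The allowance is 0.2 × 48 = 9.6 or 0.2 × 50 = 10 missed capsules. Without carry-over, at least 39 of 48 or 40 of 50 must be taken, so up to 64 − 39 = 25 or 64 − 40 = 24 may remain in the bottle.

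**The case against.** The rule says 60 although the bottle holds 64, and it speaks of prescription capsules. Read naturally, that leaves out the four grace capsules, and it may mean only doses that were due. On that view a woman who misses nothing has nothing unused in any period. If 12 of 60 is then taken as a percentage, the rule is right throughout. Averaging also rescues it: 24 spare capsules over three months is 8 per month. In addition, the article provides for a daily intake record, phone or message contact and a nutritionist's assessment at each visit, and it does not say that the capsule count alone defines the per-protocol set. A condensed article may leave the handling of a short last month to the full protocol.

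Much of this stands. The flag on perfect adherence needs the base of 64. So does any complaint about months 1 and 2, since on a base of 60 a full month agrees with 80%. A reader might infer that the rule would exclude most or all fully adherent women; the documents do not support that, because it takes the least favourable reading of the base and ignores the other adherence records.

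What does not stand is that the rule is sound as written. Scaling and averaging are not in the text, which sets the limit per month and counts each bottle. If only missed due doses are counted against a fixed 12, the error changes direction and does not vanish. Nor is this merely missing detail: a stated number disagrees with the stated bottle size, visit days, duration and criterion.

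**Conclusion.** The point holds for the last dispensing period. Unless it is scaled or averaged, the limit of 12 gives no reading that matches 80% there: it flags full adherence (base of 64), flags adherence of 94% to 98% (base of 60), or passes adherence of 75% to 76% (missed due doses only). In a full 30-day month it is right on the base of 60, and on the base of 64 it flags women at up to 85%.

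This rests on treatment ending at 84 days, as the article states; a third period of a full 30 days would remove the last-period problem. It also assumes that the count contributes to the per-protocol set, which the article implies but does not define. The intention-to-treat analysis, which keeps all women in their randomised groups regardless of compliance, is unaffected. The correction should be made before any woman's adherence is classified.

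**What to change.** Replace the fixed monthly limit by a proportion: adherence = (capsules dispensed − capsules returned) / capsules due to the actual visit date. Compute it for each dispensing period, counting capsules carried over from an earlier bottle, and overall. Class as non-adherent below the article's own 80%. Overall, 168 are due over 84 days and 0.80 × 168 = 134.4, so non-adherent means fewer than 135 taken, or more than 192 − 135 = 57 returned.

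Keep the per-period figure beside the overall one. The overall figure alone allows 168 − 135 = 33 missed capsules, so a woman could take none in the last 16 days (32 capsules) before the final blood sample and still pass. State how the two figures combine for the per-protocol set.

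The Eligibility criteria and Interventions sections must also be reconciled on bottle size, visit days, duration and how the count relates to the drop-out criterion. Whether and how that criterion is used is a clinical-management matter that this correction leaves alone.

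Cost: one sentence of wording. The return counts and visit dates are already part of the planned follow-up, so no new data are needed.
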